#### Blood draw

A blood sample for conducting genetic analyses will be collected from all participants, preprocessed, and stored at the Neuroimmunology Lab of the University Medicine Greifswald, using the cryo-preservation method. Having collected the full sample, genetic polymorphisms relevant for learning (ApoE, COMT, and BDNF) [65–68] will be analyzed at the Department of Psychiatry, Psychotherapy and Psychosomatic, University Medicine, Halle/Saale, Germany.

#### Retention and adherence

To ensure retention throughout the study, participants will be provided with information about their appointments via telephone. A letter with detailed study information and a printout of all study sessions will be sent to all participants. If applicable, the participants’ relatives will also be informed about the study and the upcoming appointments. Additionally, time and date of the next visit will be discussed at each visit. In case of not being able to attend a visit or wanting to reschedule, participants will be encouraged to leave a message on the study site’s 24/7 answering machine and will then be contacted by the study team. All study participants will receive a reasonable financial reimbursement (approximately 10 € per hour), the results of their neuropsychological screening, and, if they underwent MRI scanning, their structural MRI images on a compact disc.

Any effort to collect as much data as feasible from the participant will be made, if complete adherence to the protocol is not possible.

### Data management and monitoring

All participant data will be pseudonymized, and spreadsheets containing participant IDs as well as personal data will be secured with a password, solely known by study staff. Digital data, i.e., output files from computer-based tasks, will be stored on a secure file server directly after acquisition. Non-digitally acquired data will be manually digitalized by a member of the research staff and double-checked by another member. Progress of data entry and checking procedures will be documented. Files containing subject records will be sorted by participant ID for easy access and stored securely. Sensitive data, such as names and medical records, will be stored separately in a lockable cabinet. All digitally acquired data, e.g., output files from computer-based tasks, will be stored on a secure file server, and MRI data will be pseudonymized before analysis. Following good scientific practice, data will be stored for at least 10 years.

### Adverse event monitoring

The risk of health damage through anodal tDCS is expected to be minimal, and known adverse events (AEs) associated with the method and the study parameters (20 min, 1 mA) are restricted to tingling at the electrode sites, skin reddening under the electrode, and, less frequently, a mild headache [39]. Participants will be informed about all possible risks and about their right to withdraw consent at any time without providing cause. An adverse event questionnaire [39] will be implemented at the end of every third stimulation visit (V4, V7, V10), to monitor possible AEs at a reasonable frequency, without drawing the participant’s attention too much to stimulation-induced sensations and cause distractions from the tasks. Further, study assessors will monitor and document possible incidence of AEs and serious AEs (SAEs). In case an SAE occurs, the study physician will first make an assessment as to whether or not a causal relationship with the intervention is considered possible. If more than three of the enrolled participants suffer from SAEs that are likely to be associated with the intervention (as assessed by the study physician), the trial will be discontinued.

### Statistical analysis

Detailed analyses of primary and secondary outcomes will be reported in the statistical analysis plan to be written and registered before unblinding of investigators performing the analyses. Confirmatory analysis of treatment effects will be conducted within an intention to treat (ITT) framework with multiple imputed data sets in case of missing data (under the assumption of missing completely at random or missing at random). Further as sensitivity analyses, we will perform “per protocol” analyses, including only those participants who finished post-assessment.

Statistical analyses will be divided to analyze:
Immediate treatment effects by including all measures including V11 (post-assessment)Long-term treatment effects by focusing on V12 (1-month follow-up) and V13 (7-month follow-up).

Using linear mixed models, the measures of the letter updating task over the study period including V11 (post-assessment) will be used as dependent variable, the stimulation group (tDCS, sham) as factor, and letter updating performance at pre-assessment as well as age as covariates. The primary outcome (letter updating task score at post-assessment) will be evaluated between treatment groups based on this regression model via marginal means. We will use random intercept models that account for the clustering of measures within individuals. Secondary outcomes, i.e., performance on the second training task (Markov decision-making task) and on the transfer tasks, will be analyzed using similar statistical models. All models will be corrected for performance at pre-assessment. Structural and functional neural data will be analyzed on the whole-brain level, using general linear models, implemented in the analysis software. To assess brain-behavior associations, correlations between behavioral and neuronal parameters will be calculated. In case of violation of requirements for parametric methods, data will be transformed before analysis or appropriate non-parametric tests will be conducted. Data analysis will be conducted using IBM SPSS Statistics for Windows (IBM Corp., Armonk, NY), MatLab (The Mathworks Inc., 2016), and R software (https://www.R-project.org).

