#### Baseline measures

After providing informed consent and participating in a demographic interview, depression screening and handedness questionnaire will be administered at the baseline visit (V0). We will then assess performance in various cognitive domains (Table 1). Furthermore, the two training tasks will be performed as described above, except that at baseline, the letter updating task starts with one practice trial with 4 lists. The baseline visit will take approximately 3 h.

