### Sample size

Power calculation is based on recent studies using multi-session application of anodal tDCS during cognitive training compared to training with sham tDCS on immediate performance in the trained task (primary outcome) [11, 46, 47]. Based on these data, we estimated an effect size of 0.85. To demonstrate an effect in the primary outcome (number of correctly recalled lists in the letter updating task) with an independent *t* test using a two-sided significance level of 0.05 and a power of 80%, 46 participants (23 per group) need to be included. This conservative approach using a *t* test was chosen, even though we intend to analyze the primary outcome conducting analysis of covariance (ANCOVA) models [48]. Sample size estimation was conducted using nQuery Advisor 8.5.1 [49].

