## Methods: assignment of interventions

Allocation to anodal and sham tDCS groups will be performed using stratified block randomization. Participants will be randomly allocated by a researcher not involved in assessments. Allocation to the experimental groups (anodal vs. sham) will be performed with a 1:1 ratio with age (two age strata) and baseline and performance in the letter updating task (two performance strata) as strata. We chose cut-offs of 70 years and 2 lists correct in the letter updating task. Randomization blocks with varying block sizes will be generated for each of the four groups, using R software (http://www.R-project.org) and the blockrand package (https://CRAN.R-project.org/package=blockrand). Participants will then be allocated to the anodal or sham tDCS group, based on the generated randomization sequences within each block and stratum.

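### The primary model leaves out the V0 letter-updating score used for stratification and the SCD/MCI diagnosis; adding them is a cheap gain in efficiency and robustness, not a repair of validity

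*Protocol article*

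**What the plan says.** The Statistical analysis section plans a random-intercept linear mixed model for the letter updating task up to V11, with stimulation group as factor and "letter updating performance at pre-assessment as well as age as covariates". The V11 contrast is read from this model through marginal means. The Markov and transfer tasks get similar models, each corrected for its pre-assessment value.

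Under Methods: assignment of interventions, allocation is 1:1, "with age (two age strata) and baseline and performance in the letter updating task (two performance strata) as strata". On the cut points the article says: "We chose cut-offs of 70 years and 2 lists correct in the letter updating task".

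Participant timeline makes V0 (baseline) and V1 (pre-assessment) two separate visits, both before training. Both training tasks are already done at V0: "the two training tasks will be performed as described above, except that at baseline" a short letter-updating practice trial comes first. Each participant therefore has two pre-treatment scores on the primary outcome's own task.

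Eligibility criteria separates SCD from MCI by neuropsychological performance at baseline, so diagnosis is known for everyone. It is not a stratum and not a named covariate. Neuropsychological status appears only under Exploratory analyses.

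**The concern.** Two pieces of pre-treatment information are collected but not used in the stated model.

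- **V0 letter-updating score.** This is the measurement on which participants are stratified. A single 15-list score is a noisy baseline, and a second one can lower residual variance. A split at 2 lists balances the arms only coarsely and leaves the variation within each stratum unused.
- **SCD/MCI diagnosis.** It plausibly predicts how much a person learns in nine sessions, and nothing in the design balances it. With 23 per arm a visible imbalance can arise by chance. An adjustment added after unblinding would be post hoc, so it has to be specified beforehand. The same applies to the transfer outcomes, where diagnosis may matter more, for instance for episodic memory.

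At stake are some precision and the robustness of the result to a chance imbalance in diagnosis.

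**Working it through.** **1. The plan's own figure.** Inputs from Sample size: "we estimated an effect size of 0.85"; "two-sided significance level of 0.05 and a power of 80" per cent; "46 participants (23 per group) need to be included". A two-sample t test with the noncentral t distribution needs 22.73 per arm, hence 23 per arm and 46 in total, with power 80.5%. The figure reproduces and assumes no covariate gain.

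**2. Formulas for the covariate comparison.** Single-time-point ANCOVA at V11, in units of the outcome SD, with N = 46 and k covariates:

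- SE² = (1 − R²) × (4/N) × (1 + k/(N − k − 3)), with N − 2 − k degrees of freedom.
- V1 alone: R² = r², where r is the correlation of V0 or of V1 with V11.
- V0 and V1 together, or their mean: R² = 2r²/(1 + ρ), where ρ is the V0–V1 correlation. This treats the two visits as equally predictive.
- Age counts as a covariate in every model and is given no R² of its own.

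The article gives neither r nor ρ, so both are assumptions. The ranges are r = 0.4 to 0.7 and ρ from r up to 0.9.

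**3. Price of a covariate.** The last factor in SE² is 1 + 2/41 = 1.0488 for k = 2 and 1 + 3/40 = 1.075 for k = 3. The break-even partial R² is 1 − 1.0488/1.075 = 2.4%. For two added covariates it is 1 − 1.0488/1.1026 = 4.9%.

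**4. Worked case, r = 0.6 and ρ = 0.7.**

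- V1 + age: R² = 0.360; SE = √(0.640 × 0.08696 × 1.0488) = 0.2416.
- V0 + V1 + age: R² = 0.72/1.7 = 0.424; SE = √(0.576 × 0.08696 × 1.075) = 0.2321, a change of −3.9%.
- Mean of V0 and V1 + age: same R² with k = 2; SE = 0.2293, a change of −5.1%.

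**5. Range of SE change against V1 + age.**

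| r | ρ | V0 added | V0/V1 mean replaces V1 |
|---|---|---|---|
| 0.4 | 0.4 | −3.0% | −4.2% |
| 0.4 | 0.9 | +0.7% | −0.5% |
| 0.5 | 0.5 | −4.5% | −5.7% |
| 0.5 | 0.9 | +0.4% | −0.9% |
| 0.6 | 0.6 | −6.1% | −7.3% |
| 0.6 | 0.9 | −0.3% | −1.5% |
| 0.7 | 0.7 | −7.7% | −8.9% |
| 0.7 | 0.9 | −1.4% | −2.6% |

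**6. Power at r = 0.6.** For an illustrative true effect of 0.6 SD, the planned model has 68.0%. Adding V0 gives 73.4%, 71.4%, 69.6% or 68.1% at ρ = 0.6, 0.7, 0.8 or 0.9. At the planned effect of 0.85 and ρ = 0.7, power goes from 93.0% to 94.7%.

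**7. Diagnosis.** With 23 per arm and a fixed number of MCI participants, the hypergeometric chance that the arms differ by 5 or more (5/23 = 22 percentage points) is 10.8% for 14 MCI participants of 46, 13.0% for 18 and 23.8% for 23. The MCI share is an assumption, and any overlap of diagnosis with the strata is ignored. A difference of 5 shifts the estimate by 5/23 = 0.217 times the SCD–MCI difference in V11 that remains after V1 and age. If that difference were 0.3 SD, the shift would be 0.065 SD.

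In the worked case, adding both V0 and diagnosis changes the SE by −5.2% if diagnosis explains 5% of residual variance (power at 0.85: 93.0% to 95.1%), and by −2.7% if it explains nothing. At r = 0.4 and ρ = 0.9, adding V0 and an uninformative diagnosis raises the SE by 2.0%.

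**8. Validity of the planned model.** Simulated stratified permuted blocks (6,000 runs per setting), analyzed with V1 and age only, gave type I error of 4.4% to 5.2% and no bias. Adding the two-level V0 stratum alone changed the empirical SE by about −0.8% to +1.1%.

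**The case against.** A reader might infer that leaving out a stratification variable biases the estimate or makes the test invalid. The documents do not support that. Age is in the model, and so is the same task re-measured at V1, closer to treatment. Both stratification variables are thus represented in substance, and the simulation shows no harm. The V0 score is not thrown away either: it sets the strata and is already protected, coarsely, against imbalance.

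A reader might also infer that the extra covariates are free, or that the trial is underpowered without them. Neither holds. With 46 people a redundant covariate loses precision. The sample size rests on an unadjusted t test: "This conservative approach using a *t* test was chosen, even though we intend to analyze the primary outcome conducting analysis of covariance (ANCOVA) models".

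The size of the gain is uncertain. V0 and V1 are consecutive untreated visits, while V11 follows nine training sessions, so ρ may well exceed r. Near ρ = 0.9 the gain from V0 vanishes or reverses. The calculation is also a single-time-point approximation to a repeated-measures model.

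On diagnosis, the V1 score may already carry part of the prognostic difference, and the article quantifies no residual effect. Finally, the analysis plan, which is not shown, may add covariates.

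Most of this stands, and it limits the point to efficiency and robustness. It does not remove it: the article writes out a specific covariate list, and that list omits usable information. SCD/MCI rests on a neuropsychological battery, not on the letter updating task, so adjustment for V1 cannot be presumed to absorb it.

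**Conclusion.** The point holds as a modest recommendation. The stated model omits the continuous V0 score and the diagnosis. Adding V0 is worth somewhere between a 1% loss and an 8% gain in standard error for r = 0.4 to 0.7 and ρ from r to 0.9. Using the V0/V1 mean in place of V1 lowers it by about 0.5% to 9%, provided the two visits predict V11 equally well.

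Diagnosis is the stronger half on robustness, because neither the strata nor the listed covariates address it directly. It improves precision only if it explains more than about 2.4% of residual variance beyond the other covariates. All of these ranges rest on assumed correlations and an assumed MCI share. The planned analysis remains valid and N = 46 stands.

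**What to change.** In the analysis plan, before unblinding:

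- Replace the V1 letter-updating score by the mean of the V0 and V1 scores, which uses no extra degree of freedom. If V0 is expected to be less predictive, being the first contact with the task, enter it as a separate covariate instead, for one degree of freedom.
- Keep age and add SCD/MCI diagnosis, for one degree of freedom.
- For the Markov task, use its own V0 and V1 scores in the same way, with age and diagnosis.
- For the transfer tasks, which are first given at V1, add diagnosis only.
- Report the model with V1 and age alone as a sensitivity analysis.

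The cost is a line or two of text and one or two degrees of freedom. No new data, visits or participants are needed.

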#### Neuropsychological and behavioral assessment

Neuropsychological testing at the baseline visit (V0) comprises paper-pencil as well as computer-based assessments. Geriatric Depression Scale [40] and the Edinburgh Handedness Inventory [41] will be administered. Performance in several cognitive domains will be tested with CERAD-Plus test battery (memoryclinic.ch, [50]), digit span test [42], identical pictures task [43], and spot-a-word task [44].

The two training tasks will be performed at every visit and are descripted in detail in the “Intervention” section. Encompassing paper-pencil and computer-based assessments, the transfer tasks will be administered at pre-, post-, and follow-up visits (V1, V11–13). First, participants will perform a numeric n-back task (1 and 2 back) and the German version of the auditory verbal learning test [33, 42]. Then, participants will perform the Wiener matrices test (WMT2) in the 30-min interval to assess long-term memory [34].

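### The random-intercept-only model suits the V11 contrast badly: as written it estimates the V2–V11 average, and with a group-by-visit term it understates the V11 standard error if participants learn at different rates

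*Protocol article*

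**What the plan says.** The Statistical analysis section takes the letter updating scores over the study period up to V11 as the dependent variable. It names stimulation group as the factor and pre-assessment score and age as covariates. The V11 group difference is to be read from this model by marginal means. On the covariance it says: "We will use random intercept models that account for the clustering of measures within individuals". It names no visit term, group-by-visit term, random slope or other covariance structure.

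The Sample size section gives a different analysis for the same outcome: "we intend to analyze the primary outcome conducting analysis of covariance (ANCOVA) models".

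For the remaining outcomes: "Secondary outcomes, i.e., performance on the second training task (Markov decision-making task) and on the transfer tasks, will be analyzed using similar statistical models". The Neuropsychological and behavioral assessment section adds that "the transfer tasks will be administered at pre-, post-, and follow-up visits", that is, V1 and V11–V13. Immediate effects (up to V11) are analysed separately from V12 and V13, and all models adjust for pre-assessment. Detailed analyses are left to a statistical analysis plan, to be registered before the analysts are unblinded.

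**The concern.** A random intercept alone makes the variance the same at every visit and the correlation the same between any two visits. A training study gives reason to doubt both. If some participants improve faster than others, scores spread out over the sessions, and V11 is the last and most variable visit. The protocol itself expects such differences: learning curves are secondary outcomes, and predictors of response are an aim. A model that pools variance over V2–V11 and then draws its conclusion at V11 can claim more precision than it has. The two-sided 5% level of the confirmatory comparison is at stake.

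The transfer tasks raise a smaller question. Up to V11 each participant has one value besides the covariate, so a random intercept has nothing to separate from residual error.

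**Working it through.** **1. The plan's own figure.** Inputs from the Sample size section: effect size 0.85, "two-sided significance level of 0.05 and a power of 80"%, independent t test. With 23 per group the noncentrality is 0.85 × √(23/2) = 2.88 on 44 degrees of freedom, and power is 80.5%. With 22 per group it is 78.6%. The stated 46 is reproduced.

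**2. The model as written.** With V1 as covariate, V2–V11 give 10 scores per participant. With group as a main effect only, the marginal group difference is the same at every visit. In complete data it equals the ANCOVA contrast on the participant's V2–V11 mean. Simulated null trials gave type I error of about 4.3–5.4% at every slope SD tried. The standard error is right, but for the average over training.

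**3. The model with group-by-categorical-visit.** Assumed, since the documents give no variance components: intercept variance 0.49, residual variance 0.36, independent slopes with SD s over training, visit times 0.1, 0.2, …, 1.0 (mean 0.55, sum of squared deviations 0.825), V1 at time 0. Age is ignored in the formulas.

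- Intercept variance given V1: 0.49 − 0.49²/0.85 = 0.2075.
- Variance of a participant's mean given V1: 0.2075 + 0.55²s² + 0.36/10 = 0.2435 + 0.3025s².
- Within-participant mean square: 0.36 + (0.825/9)s² = 0.36 + 0.0917s².
- Variance the model assigns at V11: (0.2435 + 0.3025s²) + 0.9 × (0.36 + 0.0917s²) = 0.5675 + 0.385s².
- True variance at V11 given V1: 0.2075 + s² + 0.36 = 0.5675 + s².

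The SE ratio is r = √[(0.5675 + 0.385s²)/(0.5675 + s²)]. Type I error with a normal reference is 2[1 − Φ(1.96r)]. For s = 1.0, r = √(0.9525/1.5675) = 0.780. The simulation columns use 6,000 null trials per setting, 23 per arm, with V1 and age as covariates.

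| s | r | Formula | Simulated, z | Simulated, t | ANCOVA at V11 |
|---|---|---|---|---|---|
| 0 | 1.000 | 5.0% | 5.7% | 4.9% | 5.4% |
| 0.25 | 0.969 | 5.8% | 5.9% | 5.2% | 4.9% |
| 0.5 | 0.901 | 7.7% | 7.9% | 7.1% | 5.0% |
| 0.7 | 0.846 | 9.7% | 9.4% | 8.5% | 4.7% |
| 1.0 | 0.780 | 12.7% | 13.1% | 11.8% | 5.2% |

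The t reference has 42 degrees of freedom. Monte Carlo error near 5% is √(0.05 × 0.95/6000) = 0.3 percentage points.

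**4. Sensitivity.**
- Intercept–slope correlation −0.7: 4.6% at s = 0.25, 5.6% at s = 0.5, about 10% at s = 1.0.
- Other assumed components (intercept SD 1, residual SD 1, slope SD 0.05–0.20 per visit): 5.5–14.2%, or 6.4–18.6% if time enters linearly.
- Scores bounded at 15 lists (binomial, assumed start of 2 of 15, logit slope SD 0 / 0.5 / 1.0): with a V11 level of 5 or 8 lists, 7.5–8.0% / 9.4–10.1% / 12.0–13.6%. With a V11 level of 11 lists, 4.2–5.6% / 5.9–6.4% / 9.1–9.8%. ANCOVA gave 4.4–6.0% throughout.

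**5. Transfer tasks up to V11.** With 46 rows for 46 participants, only the sum of intercept and residual variance enters the likelihood. In one simulated data set the log-likelihood was −87.5406 for every intercept share tried from 0 to 0.99. The group estimate (0.020) and its SE from the total variance (0.525) were those of ANCOVA. A general-purpose mixed-model routine (not one of the packages the plan names) returned the same estimate but printed an SE of 0.496. That is a software artefact of the undetermined variance split.

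**The case against.** The strongest reply is that the inflation belongs to a model the protocol does not write down. With only the named terms, the test holds its level. A reader might infer that the 5% level fails under the plan as it stands. The documents do not support that, and the simulations contradict it. But this does not rescue the plan: the section says the model evaluates the post-assessment score, and without group-by-visit it evaluates something else.

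Second, the size is assumed. With slope SD 0.25, or with slow starters catching up, the error is near nominal, and a ceiling can make it conservative. This stands, so the range must start at about 5%.

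Third, degrees of freedom and residual covariance are ordinary content for the statistical analysis plan. Their absence from an article is no fault. The random-intercept structure, however, is stated here and not deferred.

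Fourth, a reader might infer that the transfer-task model cannot be fitted or is biased toward zero. Only the variance split is undetermined; the group effect is not. Bias toward zero would need V1 as outcome and covariate at once, with no group-by-visit term. The Secondary outcomes and Statistical analysis sections treat pre-assessment as an adjustment, which tells against that reading. Similar models also leave room for plain ANCOVA, and with two outcomes per person at V12 and V13 a random intercept is usable.

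Finally, the repeated-measures model uses V2–V10 when V11 is missing. The plan already provides multiple imputation, which can use those scores.

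**Conclusion.** The point holds conditionally. The stated random-intercept model either targets the V2–V11 average with a valid standard error or, once extended to target V11, understates the V11 standard error when learning rates differ. Under the assumed components the SE is 0 to 22% too small, and type I error runs from about 5% to 12–13% for slope SD 0 to 1.0. It is lower with a negative intercept–slope correlation, and a ceiling can reduce or reverse it. ANCOVA at V11 needs no assumption about covariance between visits and stays near 5%. All figures are for complete data without imputation. Confidence is high for the mechanism and moderate for the size. For the transfer tasks this is a wording point with no bias. The Sample size and Statistical analysis sections also name different analyses for the primary outcome. This should be settled before unblinding.

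**What to change.** Make ANCOVA on the V11 letter updating score, with pre-assessment score and age as covariates, the confirmatory analysis. Align the Statistical analysis section with the Sample size section. Put the V2–V10 scores in the imputation model so that their information is kept. This costs wording only.

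If the mixed model is kept, specify categorical visit, group-by-visit, and an unstructured or heterogeneous serial covariance or a random slope, with small-sample degrees of freedom such as Kenward–Roger. A correlated random slope adds two variance parameters. An unstructured matrix over 10 visits has 10 × 11/2 = 55, which is many for 46 participants, so name a fallback structure in advance.

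For each transfer measure name ANCOVA at V11. A single V11–V13 model with visit and group-by-visit is an alternative.

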**Fig. 2 Fig2:**
[figure not shown]
Task overview. **a** Training tasks performed at each visit. **b** Transfer tasks performed at pre-, post-, and follow-up assessments. AVLT, auditory verbal learning test [33]; WMT-2, Wiener matrices test [34]

The first training task will be a letter updating task (cf. [19]), presented on a tablet computer, and training updating of information stored in working memory. Lists of letters A to D (with lengths of 5, 7, 9, 11, or 13 letters; three times each; a total of 15 lists) will be presented in random order, one letter at a time (presentation duration 2000 ms, inter-stimulus interval 500 ms). After each list, participants will have to recall the last four letters that were presented.

Second, participants will be presented with a three-stage Markov decision-making task on a laptop computer (cf. [24, 35, 36]), where they have to choose between two actions, i.e., pressure of left or right key, which results in an action-related reward (monetary gain or loss). The underlying Markov probability defines that a decision at a given state determines not only the reward, but also the transition into the next out of three decisional stages. This requires the participants to learn choosing the optimal sequence of action to maximize overall gains, minimize overall losses, and thus continuously transition through all three stages. There will be two different learning conditions. In the *immediate reward condition*, the action-outcome associations will be equal for all three stages. Here, the optimal choice is always associated with a gain (+ €0.05), whereas choosing the other alternative results in a loss (− €0.05). In the *delayed reward condition*, the action-outcome associations will vary over the three stages. An optimal action choice will be related to a small loss (− €0.05) in the first two stages and a larger gain (+ €0.25) in the third stage. A chain of suboptimal action choices however will result in a small gain (+ €0.05) in the first two stages and a large loss (− €0.25) in the third stage.

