#### Primary outcomes

The primary outcome measure will be working memory performance at post-assessment, as measured by the number of correctly recalled lists in the letter updating task.

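### The fallback sentence lets the primary analysis change to a transformation or an unnamed non-parametric test; the primary outcome should be exempt from it

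*Protocol article*

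**What the plan says.** The Statistical analysis section of the protocol article sets up the confirmatory comparison as a random-intercept linear mixed model with "the stimulation group (tDCS, sham) as factor, and letter updating performance at pre-assessment as well as age as covariates". The primary outcome "will be evaluated between treatment groups based on this regression model via marginal means", and the same section adds that "All models will be corrected for performance at pre-assessment".

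Under Primary outcomes, the endpoint is "working memory performance at post-assessment, as measured by the number of correctly recalled lists in the letter updating task". The task description under Intervention gives five list lengths, "three times each; a total of 15 lists", so the score is an integer from 0 to 15. The only hint of its level is in the section on assignment of interventions: "We chose cut-offs of 70 years and 2 lists correct in the letter updating task".

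Later in the Statistical analysis section comes the sentence at issue: "In case of violation of requirements for parametric methods, data will be transformed before analysis or appropriate non-parametric tests will be conducted". It is worded for all data and all parametric methods. The section also defers detail to a "statistical analysis plan to be written and registered before unblinding of investigators performing the analyses"; that plan is not at hand.

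**The concern.** A confirmatory comparison should be one analysis, known in advance. The fallback makes it conditional: the raw-scale adjusted model stands if a check is passed, and otherwise either a transformed analysis or a non-parametric test replaces it.

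The replacements do not answer the same question. A transformation keeps the covariates but moves the effect off the scale of lists recalled. A standard two-group rank test gives no marginal-mean difference and uses neither the pre-assessment score nor age. Two things are therefore at stake: power, if the adjustment is dropped, and type I error, if the choice among analyses is made with the outcome data in view.

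**Working it through.** **1. The plan's own figure.** Inputs from the Sample size section: standardised effect 0.85, two-sided alpha 0.05, power 80%, independent t test. The noncentral-t calculation gives n = 22.73 per arm, rounded up to 23, so 46 in total; power at 23 per arm is 80.5%. The stated 46 reproduces, and no covariate is needed to reach it.

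**2. Cost of an unadjusted rank test at the planning effect.** The article gives no pre-post correlation rho, so a range is assumed. Adjustment raises the effective effect to 0.85/√(1 − rho²); for rho = 0.5 that is 0.85/√0.75 = 0.98. Under normality the Mann-Whitney test has relative efficiency 0.955, so 23 per arm act as 23 × 0.955 = 21.97, with power of about 78.6%. It would need 22.73/0.955 = 23.8, that is 24 per arm, for 80%.

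| rho (assumed) | Adjusted power | Loss against 78.6% |
|---|---|---|
| 0 | 80.5% | 1.9 points |
| 0.3 | 84.0% | 5.4 |
| 0.5 | 90.2% | 11.6 |
| 0.6 | 94.1% | 15.5 |
| 0.7 | 97.7% | 19.1 |

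**3. Simulation on a 0 to 15 count.** There were 2,500 runs per row, 23 per arm. Scores are binomial with 15 lists and a logit-normal person effect (SD 1.3). The mean baseline is 2.8 lists, with 58% of participants at or below 2. In scenario A post-training scores stay low (mean 3.4 without an effect). In B and C they move to mid-range (mean about 6.6). Observed pre-post correlations without an effect are 0.61, 0.59 and 0.44. All of these are assumptions. The models adjust for the pre-assessment score at a single visit; they are not the full mixed model.

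No treatment effect (rejection rates):

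| | A | B | C |
|---|---|---|---|
| Shapiro-Wilk on ANCOVA residuals significant | 54.8% | 15.0% | 16.4% |
| ANCOVA, raw score | 5.1% | 5.7% | 4.9% |
| Mann-Whitney, unadjusted | 5.1% | 5.5% | 4.9% |
| Check, then Mann-Whitney if it fails | 6.0% | 6.0% | 5.0% |
| Smallest p of raw, arcsine, Mann-Whitney | 9.4% | 9.6% | 8.0% |

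The Monte Carlo standard error at 5% is √(0.05 × 0.95/2500) = 0.44 points, so the ANCOVA rates are compatible with 5%.

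Effect of 0.9 on the logit scale (power):

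| | A | B | C |
|---|---|---|---|
| Shapiro-Wilk on ANCOVA residuals significant | 30.4% | 6.9% | 7.8% |
| ANCOVA, raw score | 70.1% | 70.0% | 61.7% |
| Arcsine ANCOVA | 69.2% | 72.0% | 62.4% |
| Rank ANCOVA | 65.9% | 71.2% | 60.8% |
| Mann-Whitney, unadjusted | 50.7% | 51.9% | 52.9% |
| Check, then Mann-Whitney if it fails | 65.0% | 68.8% | 61.0% |

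ANCOVA minus Mann-Whitney is 19.4, 18.1 and 8.8 points. ANCOVA minus check-then-switch is 5.1, 1.2 and 0.7 points. Power is below 80% throughout because this effect is smaller than the planning effect: an unadjusted t test has only 53-55% here. The differences between methods are what matters.

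**4. Further simulation under other assumed distributions, same arm size.** Raw ANCOVA had type I error of 4.6-5.7%, and HC3 (heteroscedasticity-robust) standard errors 3.9-4.9%. The loss from an unadjusted Mann-Whitney test was about 8-23 points. Free choice among three tests gave 7-10% type I error, and a fixed check-then-switch rule stayed near 5%.

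**The case against.** The strongest reply is that the diagnostic, the trigger and the named fallback belong in the SAP, which the article promises before the analysts are unblinded. That is right as far as it goes: their absence from a journal article is no fault. If the SAP fixes one rule, the 7-10% figure does not apply, because a fixed rule stays near 5-6%. What remains is what the sentence does state, namely that the primary test is conditional on the data. A SAP that repeated it would leave the choice open after registration. Masked arm labels help only in part, since a two-sided p-value is the same whichever arm is called A.

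The sentence also follows the imaging and correlation analyses and might be meant for those. Its wording does not say so.

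Four stronger readings are tempting, and the article does not support them.

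- **That the switch is likely.** The cut-off of 2 lists is a baseline value; the primary score follows nine training visits on the same task. A linear model needs suitable residuals, not a normal raw score. Across the simulations the check failed in about 6% to 55% of trials, depending on the assumed post-training level and effect.
- **That the switch would discard the adjustment.** A transformation keeps the covariates, as does rank ANCOVA, with little or no loss of power in most scenarios (about 4 points in scenario A). The section requires correction for pre-assessment in all models, and it names no unadjusted test.
- **That the trial has no reserve for this.** It is sized on an unadjusted t test, which the article itself calls conservative. Even the unadjusted rank test keeps about 78.6% at the planning effect under normality.
- **That a rank test cannot be used with multiple imputation.** The article gives no basis for this; rank statistics can be computed in each imputed data set and pooled.

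**Conclusion.** The point holds in a limited form. The plan allows its confirmatory analysis to be replaced after an assumption check, by methods that may change the scale, the contrast and the covariate adjustment. It permits these losses and does not prescribe them.

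The size depends on how the sentence is used. If it led to an unadjusted Mann-Whitney test, the cost would be roughly 8 to 23 power points against adjusted ANCOVA. If the choice were left free, type I error would be about 7-10%. If one rule were fixed beforehand, type I error would be near 5-6%, with about 1 to 5 power points lost in the tabulated scenarios. These figures rest on assumed score distributions, an assumed pre-post correlation and a single-visit ANCOVA in place of the mixed model.

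The switch buys nothing needed for validity: in every simulated scenario, adjusted ANCOVA on the raw count kept its type I error close to 5%. The defect is moderate and cheap to remove, and it does not put the sample size or the primary model in doubt.

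**What to change.** Exempt the primary outcome from the fallback sentence, in the protocol and in the SAP registered before unblinding:

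- The single primary analysis is the difference in lists recalled at post-assessment, adjusted for pre-assessment score and age, on the raw scale, whatever the residual check shows.
- Name one inference method for it, for example HC3 standard errors. HC3 is defined for a single-visit regression. If the contrast comes from the repeated-measures model, name the participant-level robust equivalent with a small-sample correction. Choose one; do not leave alternatives open.
- Report a transformed analysis, a covariate-adjusted rank analysis or a binomial model (lists correct out of 15) only as prespecified sensitivity analyses that cannot replace the primary result.
- Confine the transform-or-rank option to other outcomes, with a covariate-adjusted method named where pre-assessment correction is required.

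The cost is a few sentences in each document and no change to conduct or sample size. The statistical price is a slight loss of power from robust standard errors, about 2-3 points in simulation.
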